### Participants

Participants will be adults residing in the Autonomous Community of Aragon (Spain) who have been diagnosed with long COVID-19 and meet criteria for at least one comorbid emotional disorder. Recruitment will take place at Hospital Royo Villanova from Zaragoza, Spain. An online dissemination campaign will also be conducted through social medial and in collaboration with the Long COVID-19 association from Aragón. Eligibility criteria to participate in the study are reported in Table 1. Participants will not be involved in the design, conduct or reporting the trial.

**Table 1 pone.0342908.t001:** Inclusion and exclusion criteria to participate in the randomized controlled trial.

Inclusion criteria	Exclusion criteria
Residing in the Autonomous Community of Aragon (Spain). Being at least 18 years old. Understanding of Spanish. Being diagnosed with long COVID-19: documented SARS-CoV-2 infection and persistence of symptoms beyond 12 weeks after the acute infection. Symptoms of depression (ODSIS≥7) and/or anxiety (OASIS≥8). Meeting the criteria for an emotional disorder diagnosis. Having access to the Internet. Signing the informed consent.	Pre-existing emotional symptoms prior to the acute SARS-CoV-2 infection. Currently receiving psychological treatment. Having a diagnosis of severe mental disorder (e.g., personality disorder, bipolar disorder, etc.). Active suicidal ideation at the time of the assessment. Individuals on psychotropic medication must maintain their dosage throughout the study, unless medically contraindicated.

Using the G*Power software [23], and taking into account the two study conditions, the five assessment points (pre-treatment, post-treatment, and follow-ups at 3, 6, and 12 months), as well as the statistical models planned for data analysis, we calculated a total sample size of 74 participants, achieving a statistical power of 90%, an alpha level of 0.05, and an effect size of 0.30. Considering an anticipated dropout rate of 20%, the required sample size is estimated at 45 participants per condition (total sample size = 90 participants).

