### Data analysis

First, descriptive statistics of clinical psychological diagnosis, sociodemographic, and long COVID-19 symptoms will be explored to characterize the sample at baseline. Means and standard deviations for psychological measures (i.e., ODSIS, OASIS, etc.) at pre-treatment will also be calculated to provide a baseline description of our sample.

Second, the main effect of time, group and time x group interaction will be analyzed. Several linear mixed-effects models will be employed for each dependent variable to be analyzed (i.e., primary outcomes such as anxiety and depressive symptoms; secondary outcomes such as memory failures, emotional regulation difficulties, etc.). For each of these models, Time (within-subject variable; T1 vs. T2 vs. T3 vs. T4 vs. T5) and Experimental Group (between-subject variable; Experimental vs. Waitlist) will be included as fixed effects. Random slopes for participants will also be considered and included as random effects in the model. The models will have the following structure: [Dependent Variable ~ Time × Experimental Group + (1|Participant)].

In participants from the experimental group, descriptive analyses will also be conducted to assess their neuropsychological and cognitive status, as well as stress levels (hair cortisol and cortisone), prior to starting the intervention. Repeated measures ANOVAs with time as the within-subject factor will be performed to determine whether changes occur in these variables over time (i.e., after the intervention and at 3 and 12-months follow up). Exploratory correlational analyses will be conducted to examine associations between hormonal levels and other dependent variables. Subsequently, multiple linear regression analyses will be performed to determine which hormonal variables significantly predict subjective cognitive complaints, objective cognitive performance, and emotional variables, while controlling for relevant covariates (e.g., age and educational level).

Satisfaction with the intervention will be summarized using means and standard deviations derived from the satisfaction questionnaire. Additionally, adherence to the intervention will be calculated as the proportion of attended sessions relative to those scheduled.

Analyses will be conducted using the lme4 package (version lme4_1.1–13; [46]) in R statistical software (version 4.1.0; [47]) and SPSS v25.0 [48].

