Despite the results of this study may have important clinical implications, we need to also acknowledge certain limitations. First, participants and researchers cannot be blinded to the intervention assignment, which may introduce expectancy effects. To minimize this potential bias, online assessments will be conducted so that the researchers are not involved in evaluating the efficacy of the intervention. Second, although sample size has been estimated to be sufficient to detect moderate effects, it may limit generalizability to broader populations or to patients with higher or lower long COVID-19 severities. Third, digital literacy of potential participants may interfere or even impede their participation in the study. For instance, participants may present difficulties to engage with the online platform to respond to the psychological assessments or they may find difficulties to engage in the online sessions through videocalls. These potential technology-related challenges will be partially mitigated by the support of the therapist who will explain the procedures for completing the assessment protocol and engaging in the online sessions. Additionally, satisfaction questions regarding the online format will also be included to capture participants’ opinion about the intervention and to evaluate whether these issues have been adequately addressed. Related with participants’ interest in this study, it is possible that some participants may show reluctance when asked to provide a hair sample. To minimize this potential concern, the research team will explain to participants that the hair sample consists of collecting only 5–6 strands from the back of the head and it will not affect their physical appearance. Finally, another potential limitation is that, for ethical reasons, participants in the control group will be offered the opportunity to join in the experimental group after completing the post-treatment assessment. Consequently, only the experimental group will be available for follow-up assessments, and comparisons between groups will be limited to the post-treatment time point.

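### The random-slopes sentence contradicts the printed random-intercept formula, and that formula turns the only between-arm test into an inefficient change-score comparison whose standard error relies on equal correlation across all waves

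*Protocol article*

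**What the plan says.** The Data analysis section of the protocol article sets one mixed model for each outcome and says that "the main effect of time, group and time x group interaction will be analyzed". Time is a categorical factor: "Time (within-subject variable; T1 vs. T2 vs. T3 vs. T4 vs. T5". On the random part it says "Random slopes for participants will also be considered and included as random effects in the model". The formula that closes the paragraph is "Dependent Variable ~ Time × Experimental Group + (1|Participant", and the section adds "Analyses will be conducted using the lme4 package".

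Two other places bear on this. The Procedures section has participants complete the pre-treatment assessment before they learn their arm. The Discussion says that "only the experimental group will be available for follow-up assessments, and comparisons between groups will be limited to the post-treatment time point".

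**The concern.** In lme4 notation, (1|Participant) is a random intercept and nothing more. Two analysts working from this paragraph could fit different models to both primary outcomes.

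Two features of the printed formula also affect the randomised comparison.

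- **Free baseline means.** Time × Group gives each arm its own T1 mean, although the expected T1 means are equal by randomisation. With complete data the T2 interaction is then the difference in mean change from T1, which makes poor use of baseline.
- **One residual variance for all waves.** Controls contribute T1 and T2; the experimental arm contributes T1 to T5, over about 15 months (12 weeks plus 12 months). The standard error of the T2 contrast therefore borrows from T3 to T5 of one arm. That is correct only if every pair of waves has the same correlation.

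At stake are power that the trial could have at no data cost, and an error rate for the main test that depends on an unstated covariance pattern.

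**Working it through.** **Inputs.** From the document: 1:1 allocation, five waves, N = 74 before dropout, 90 after, alpha 0.05, effect size 0.30. Assumed, because the document does not give them: all correlations; equal variance at each wave unless stated; and effect size 0.30 read as Cohen's f, so d = 2 × 0.30 = 0.60.

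**1. The plan's own figure.** The Participants section bases its calculation on "the two study conditions, the five assessment points (pre-treatment, post-treatment, and follow-ups at 3, 6, and 12 months". Its result reads "we calculated a total sample size of 74 participants, achieving a statistical power of 90%, an alpha level of 0.05, and an effect size of", the value being 0.30. A repeated-measures between-groups F test with m = 5 and an assumed rho of 0.5 has noncentrality f²Nm/(1+(m−1)rho) = 0.09 × 74 × 5 / 3 = 11.1 on 1 and 72 df. Power is 0.908, so 74 is reproduced. That test averages the arms over five waves; it is not the T2 contrast.

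**2. Could the promised slopes be fitted?** A slope on factor Time, (Time|Participant), needs 74 × 5 = 370 random effects. Complete data at all waves would give 370 observations. With controls at T1 and T2 only there are 37 × 5 + 37 × 2 = 259. Neither leaves anything to identify a separate residual.

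**3. Efficiency at T2** (outcome SD 1). The per-person variance is 2(1−rho) for a change score and 1−rho² with baseline adjustment; the ratio is (1+rho)/2. The standard error is √(variance × 2/37), and power comes from the noncentral t.

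| rho | Change variance | Adjusted variance | Ratio | Power, change | Power, adjusted |
|---|---|---|---|---|---|
| 0.3 | 1.40 | 0.91 | 0.65 | 58% | 76% |
| 0.5 | 1.00 | 0.75 | 0.75 | 72% | 84% |
| 0.7 | 0.60 | 0.51 | 0.85 | 91% | 95% |

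The ratio assumes equal T1 and T2 variances. If entry cut-offs halved the T1 variance, at rho 0.5 the change variance would be 0.5 + 1 − 2 × 0.5 × √0.5 = 0.793 against 0.75. The ratio would be 0.95 and the gain small.

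**4. Standard error of the T2 contrast.** The model's residual is roughly a weighted mean of 1 minus the average correlation in each arm, with weight 4 for the five-wave arm and 1 for the two-wave arm. The correct value is 1 − corr(T1,T2). For baseline/follow-up correlations of 0.5/0.75:

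- The average over the ten pairs is (4 × 0.5 + 6 × 0.75)/10 = 0.65.
- The pooled residual is (4 × 0.35 + 0.50)/5 = 0.38, against a correct 0.50.
- The standard error ratio is √(0.38/0.50) = 0.87.
- Type I error is P(|Z| > 1.96 × 0.87), about 8.7%.

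| Assumed pattern | Pooled | Correct | SE ratio | Type I, by hand | Type I, simulated |
|---|---|---|---|---|---|
| Equal, 0.5 | 0.500 | 0.50 | 1.00 | 5.0% | 5.1% |
| 0.5/0.65 | 0.428 | 0.50 | 0.93 | 7.0% | 7.0% |
| 0.5/0.75 | 0.380 | 0.50 | 0.87 | 8.7% | 8.6% |
| 0.4/0.7 | 0.456 | 0.60 | 0.87 | 8.7% | 8.8% |
| AR(1) 0.7 | 0.444 | 0.30 | 1.22 | 1.7% | 1.8% |

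The simulations used 20,000 null trials of the printed model, 37 per arm. Repeat runs agreed within about one percentage point. With person-specific linear slopes (SD 0.03 to 0.08 per month) the T2 test was conservative, at 4.5% down to 3.3%.

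**5. Late within-arm contrast, T5 minus T1.** Under AR(1) 0.7 the correct value is 1 − 0.7⁴ = 0.760 against 0.444 pooled. The ratio is 0.76 and type I error about 13% (12.6% simulated). Slope SDs of 0.05 and 0.08 gave 9.5% and 14.5%. It can also go the other way: with T1 variance halved under equal correlation it was 3.5%.

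**The case against.** The strongest reply is that the formula is explicit, so the slopes sentence may be a slip for random intercepts, and that Time × Group with free baseline means is a standard, valid analysis. Much of this stands. Under randomisation the T2 interaction is unbiased, so the baseline point concerns efficiency, not error. The slip reading is plausible, but the text still states two models and needs correcting.

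Three stronger readings are tempting and not supported.

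- **That the standard errors are wrong.** They are right under equal correlation, and otherwise may be too small or too large. The document gives no covariance, so neither direction can be asserted.
- **That random slopes cannot be fitted at all.** This holds for slopes on factor Time. The text does not say what the slope is on, and a slope on numeric time could be specified.
- **That power is known to rise by 12 points.** That is one row of the table. The gain is about 18 points at rho 0.3 and 4 at rho 0.7. It also rests on reading 0.30 as Cohen's f, a metric the document does not name.

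It is also fair that the T2 standard error problem comes only from putting T3 to T5 in the same fit. A random intercept fitted to T1 and T2 alone gives the ordinary change-score standard error.

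**Conclusion.** The contradiction between text and formula is certain. So is the change-score form of the T2 test with complete data. With equal variances, its variance could be cut to (1+rho)/2, a saving of 15% to 35% for rho from 0.7 to 0.3, using data the trial already collects.

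The error-rate finding is conditional. The nominal 5% holds under equal correlation. Under the alternatives tried it ranges from about 2% (AR(1) 0.7) to 9% (follow-ups more correlated with each other than with baseline). Late within-arm contrasts, which carry the maintenance hypothesis in the Introduction, reached 14.5%. These figures show sensitivity to an unstated assumption; they do not predict this trial's error rate. The change is worth making because it removes that dependence and usually adds power.

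**What to change.** Replace the random-slopes sentence and the formula with one stated model. Either of these serves, and with complete data they are equivalent for the T2 effect:

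- A constrained longitudinal analysis with a common T1 mean for both arms, categorical time and an unstructured within-participant covariance, reporting the T2 arm difference.
- A comparative model restricted to T1 and T2, with T2 as outcome and T1 as covariate.

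The article describes no separate within-arm model for the survey outcomes. If T1 to T5 contrasts in the experimental arm are reported for them, state that model too and use an unstructured covariance.

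The cost is a rewritten paragraph and a different R function, for example a gls or mmrm-type fit in place of the printed lme4 call. No data collection changes. The Trial status section places analysis after data collection is complete, so the change can be fixed beforehand and notified through the amendment route in Procedures.

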## Methods

### Design

This study protocol describes a two-arm parallel superiority RCT (allocation ratio 1:1). The trial has been designed to test the superiority of the experimental treatment (the UP) over the control condition (waiting list control group) in the improvement of depressive and anxiety symptoms, memory failures, dimensions of emotional disorders, emotional dysregulation, perceived stress, quality of life, distress tolerance and positive temperament in long COVID-19 participants.

The randomization sequence will be generated using the online platform randomizer.org to establish the order of group assignment (e.g., participant 1 = control; participant 2 = control; participant 3 = experimental; participant 4 = control; participant 5 = experimental; participant 6 = experimental…participant 90 = control). As participants enroll in the study, they will be assigned to the experimental or control group following this predefined sequence. Since the control group will remain on the waiting list for 12 weeks, participants cannot be blinded to their assignment condition. For the same reason, the researchers will also be aware of participants’ group assignments.

To ensure the transparency and methodological rigor of the study it was registered in clinicatrials.gov (registration identifier: NCT06928480; date of registration: May 22, 2025). Additionally, this study protocol adheres to the Standard Protocol Items: Recommendations for Interventional Trials (SPIRIT checklist [22]; see supporting information S1 Checklist).

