
### Intervention

#### Experimental group.

Participants assigned to the experimental condition will receive the UP in group format. The UP is a transdiagnostic CBT intervention composed of eight modules designed to train participants in emotion regulation skills [45]. In this study these eight modules will be distributed to be applied through 12 online sessions (videocalls). The distribution of the sessions can be consulted in Table 2. The sessions will be conducted by a research team trained in the UP (Level II certification) and supervised by a clinician with Level III UP certification. In addition, treatment fidelity to the UP will be monitored throughout the course of the sessions.

**Table 2 pone.0342908.t002:** Distribution of the UP sessions.

UP modules	Sessions
1. Setting goals and maintaining motivation	1
2. Understanding emotions	2 - 3
*3. Mindful emotion awareness*	4 - 5
*4. Flexible thinking*	6 - 7
*5. Emotional behaviors*	8
*6. Facing physical sensations*	9
*7. Emotional exposures*	10 - 11
8. Relapse prevention	12

Note: the five core UP modules have been indicated in italics.

The first session will serve to introduce the program’s characteristics, to present the research team members (therapist and co-therapist) and provide an opportunity for participants to get to know each other. After this introduction, the content of the session (i.e., setting goals and maintaining motivation) will be presented. Subsequent sessions (i.e., from the second to the twelve session) will follow the same structure: during the first hour, exercises from the previous week will be reviewed. The second hour will include the introduction of the new module’s content, the practice of the corresponding module exercises, and the assignment of the exercises to be completed during the week. After each module (at the end of sessions 1, 3, 5, 7, 8, 9, 11, and 12), the true/false questions proposed in the UP will be administered to ensure that participants have correctly acquired the basic knowledge of the module.

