The provision of the psychological intervention in an online group format constitutes also an innovative and cost-effective approach that will also help to overcome practical and clinical challenges found in long COVID-19 patients. Previous studies have indicated that long COVID-19 patients often report fatigue, muscle paint, general pain and joint pain [4] which may impede travelling to onsite healthcare centers to receive in-person attendance. Thus, online sessions will increase accessibility to psychological care in long COVID-19 populations. As for the group format of delivery it may facilitate peer support and shared learning experiences in health conditions [54]. On the other hand, many individuals with long COVID-19 often report feelings of loneliness, stigmatization and discrimination [55–58] and the group format may provide an opportunity to normalize and validate symptoms and to reduce social isolation. In fact, a recent systematic review indicated that people with long COVID-19 frequently use social media forums and online groups to connect with peers who have similar experiences [59]. Also importantly, the program has been designed considering the cognitive and physical limitations of long COVID-19 individuals, including scheduled breaks to help them to participate fully with the sessions. We expect that these patient-focused adaptations will help to facilitate engagement throughout the program, which should in turn contribute to high levels of satisfaction with the intervention. Taken together, these features not only improve accessibility and engagement but also have important clinical implications, as they provide a patient-centered model of psychological care that can be readily implemented in healthcare settings to address the emotional and social needs of long COVID-19 patients.

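### UP is delivered in therapy groups, but the stated model and sample size treat participants as independent; if outcomes correlate within groups, the post-treatment between-arm standard error is too small

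*Protocol article*

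**What the plan says.** The Design section describes a "two-arm parallel superiority RCT (allocation ratio 1:1", with individuals assigned from a pre-generated sequence. For the intervention, "Participants assigned to the experimental condition will receive the UP in group format". Procedures and the Experimental group section give 12 two-hour online sessions with a therapist and co-therapist, and further group sessions at the 3-, 6- and 12-month follow-ups. Controls receive no psychological intervention for 12 weeks, complete the post-treatment assessment, and may then join the experimental programme. The Discussion limits between-group comparison to post-treatment.

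On the analysis, Data analysis states: "The models will have the following structure: [Dependent Variable ~ Time × Experimental Group + (1|Participant". The factor called Experimental Group there is defined as Experimental versus Waitlist, so it is the trial arm and not the therapy group. The same paragraph adds that participant random slopes will be considered. It mentions no other random effect.

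The Participants section says "we calculated a total sample size of 74 participants, achieving a statistical power of 90"%, with "an alpha level of 0.05, and an effect size of 0.30", taking into account the two conditions and "the five assessment points (pre-treatment, post-treatment, and follow-ups at 3, 6, and 12 months"). It continues: "Considering an anticipated dropout rate of 20%, the required sample size is estimated at 45 participants per condition". No ICC, design effect, group size or number of therapy groups is given.

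**The concern.** This is a partially nested design: treated participants share sessions and fellow members, and controls share nothing before T2. The Discussion itself gives a reason to expect correlated outcomes, since "the group format of delivery it may facilitate peer support and shared learning experiences". A participant random intercept handles repeated measures on one person. It cannot represent correlation between different people in the same group, and neither can participant random slopes.

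If such correlation exists, the treated-arm mean at T2 varies more than the model believes. The standard error of the arm comparison is then too small, intervals are too narrow, and false positives are more frequent than 5%. Because T2 is the only between-arm time point, that standard error carries the superiority claim for both primary outcomes and for every secondary outcome compared between arms.

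**Working it through.** **Inputs from the article.** Alpha 0.05, effect size 0.30, power 90%, N = 74, five assessments, 45 per arm.

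**Assumptions, because the article is silent.** The effect size is Cohen's f (G*Power is used), the correlation between assessments is ρ = 0.5, therapy-group size is c = 6 to 10 and ICC is 0.01 to 0.10. With 45 treated participants these sizes mean 45/10 = 4.5 to 45/6 = 7.5, that is 5 to 8 groups.

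**Step 1: reproduce the stated N.** The between-factors F test for repeated measures has noncentrality λ = f²·N·m/(1 + (m−1)ρ) on 1 and N−2 degrees of freedom. With N = 74 and m = 5, λ = 0.09 × 74 × 5/3 = 11.1 and power is 90.8%. At N = 72 power is 89.99%, so 74 is the smallest even total reaching 90%. The stated figure is reproduced, and the calculation treats all participants as independent.

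**Step 2: standard error and type I error.** With clustering in the treated arm only, the design effect there is DE = 1 + (c−1)·ICC. The true SE divided by the model SE is r = √((DE + 1)/2). The shortfall of the model SE is 1 − 1/r, and the actual two-sided type I error is 2·(1 − Φ(1.96/r)). For c = 8 and ICC 0.05: DE = 1.35, r = √1.175 = 1.084, shortfall 7.7%, type I error 7.1%.

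| c | ICC | DE | r | Model SE too small by | Type I error |
|---|---|---|---|---|---|
| 6 | 0.01 | 1.05 | 1.012 | 1.2% | 5.3% |
| 8 | 0.01 | 1.07 | 1.017 | 1.7% | 5.4% |
| 10 | 0.01 | 1.09 | 1.022 | 2.2% | 5.5% |
| 6 | 0.05 | 1.25 | 1.061 | 5.7% | 6.5% |
| 8 | 0.05 | 1.35 | 1.084 | 7.7% | 7.1% |
| 10 | 0.05 | 1.45 | 1.107 | 9.6% | 7.7% |
| 6 | 0.10 | 1.50 | 1.118 | 10.6% | 8.0% |
| 8 | 0.10 | 1.70 | 1.162 | 13.9% | 9.2% |
| 10 | 0.10 | 1.90 | 1.204 | 17.0% | 10.4% |

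**Step 3: simulation check.** 40,000 null trials per setting, 45 per arm, with the group effect placed at T2 in the treated arm only. With two complete time points, the Time × Arm test in the random-intercept model is a t test on change. At ICC 0 the rejection rate was 4.8–5.2%. With pre–post correlation 0.5 and groups of 6, 8 and 10 it was:

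- ICC 0.01: 5.3%, 5.6%, 5.7%
- ICC 0.05: 6.3%, 6.9%, 7.6%
- ICC 0.10: 7.8%, 9.0%, 10.0%

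These agree with the formula. With pre–post correlation 0.7 the rates rise to 7.4–9.1% at ICC 0.05 and 9.8–13.9% at ICC 0.10. Change scores then vary less (variance 2 × 0.3 = 0.6 instead of 2 × 0.5 = 1), so the same group effect is a larger share of them.

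**Step 4: power once clustering is modelled.** Divide λ by (DE + 1)/2, at N = 74 and c = 8:

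- ICC 0.01: 11.1/1.035 = 10.72, power 89.8%
- ICC 0.05: 11.1/1.175 = 9.45, power 85.8%
- ICC 0.10: 11.1/1.35 = 8.22, power 80.8%

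This is a large-sample correction. Having only 5 to 8 groups would lower power further.

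**The case against.** The strongest objection is that the harm is conditional. The Discussion says only that the group format may foster peer support, which makes correlation plausible but does not measure it. A reader might infer from the missing term that type I error certainly exceeds 5%. The documents do not support that: at ICC 0 there is no excess, and at 0.01 it is about half a percentage point. This objection stands, so the point is worded conditionally.

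A reader might also count the therapist pair as a second source of clustering. Procedures refers to one psychologist responsible for both the interview and the programme, and nothing shows that different pairs lead different groups. If the same staff lead every group, they add no between-group variance. The point therefore rests on the shared group alone.

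The formula may be schematic: participant slopes are mentioned just before it but do not appear in it. A fuller analysis plan might say more. This carries limited weight, because the article commits to an explicit structure and nowhere hints at a therapy-group term.

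Finally, the check uses T1 and T2 only, while the planned model spans T1 to T5. Since between-arm comparison is limited to T2, this is the relevant contrast, and adding later records does not supply the missing group term.

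**Conclusion.** The point holds conditionally. The absence of any clustering term or allowance is plain from the text. The direction of the bias is certain for any positive within-group correlation, but its size is not fixed by the documents.

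Over assumed groups of 6 to 10, the model SE is too small by about 1–2% at ICC 0.01, 6–10% at 0.05 and 11–17% at 0.10. The matching type I errors are about 5.3–5.5%, 6.5–7.7% and 8.0–10.4%. The power figures also rest on reading the effect size as f and on the assumed ρ of 0.5. They show the sensitivity of the article's own calculation and do not demonstrate that the trial is underpowered.

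This is a moderate weakness in the main comparison that should be put right before analysis.

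**What to change.** Record a therapy-group identifier for every treated participant. Make the primary between-arm T1–T2 analysis partially nested: a random therapy-group effect acting only on experimental-arm post-baseline records, with each control as its own cluster. In lme4 this means adding `(0 + UPpost | TherapyGroup)`, where `UPpost` is 1 for those records and 0 otherwise. Use Satterthwaite or Kenward–Roger degrees of freedom. Report the estimated ICC, and restate power over a stated range of ICC and group size without enrolling more participants.

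Controls may join UP groups after T2. If their later records enter any model, their therapy group must be coded as well; if not, say so.

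The cost is one recorded variable, one model term and wider intervals. With about 5 to 8 groups the variance component will be imprecise and may be estimated at zero, which would return the planned model. Add a sensitivity analysis that repeats the T2 comparison with the ICC fixed at several values, for example 0.01, 0.05 and 0.10. Recruitment is expected to run to the end of 2026 with analysis afterwards, so the change can still be made before any outcome analysis.
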